## 7.7 Premature termination of the study

It is possible that the study shows that topical rapamycin has no effect or worsens the skin lesions. In that case, we will terminate the study prematurely. Another reason for terminating the study prematurely is when emerging adverse events are of such serious nature that continuation of the trial becomes unacceptable.

If the study is terminated, patients will be followed-up and treated according to accepted standards of care.

# 8. SAFETY REPORTING

## 8.1 Section 10 WMO event

In accordance to section 10, subsection 1, of the WMO, the investigator will inform the subjects and the reviewing accredited METC if anything occurs, on the basis of which it appears that the disadvantages of participation may be significantly greater than was foreseen in the research proposal. The study will be suspended pending further review by the accredited METC, except insofar as suspension would jeopardise the subjects’ health. The investigator will take care that all subjects are kept informed.

## 8.2 Adverse and serious adverse events

Adverse events are defined as any undesirable experience occurring to a subject during a clinical trial, whether or not considered related to the investigational drug. All adverse events reported spontaneously by the subject or observed by the investiga­tor or his staff will be recorded.

When there is a possible adverse event, the trial physician will consult the PI who will then take appropriate action based on his assessment. An example of an adverse event related to the investigational drug (an adverse reaction) is local irritation after application of rapamycin. If this is not allergic, the trial will continue and the patient will get a corticosteroid temporarily. When local irritation is based on an allergic reaction the patient will be excluded.

When a local side effect appears, the affected side of the face will be recorded on the study forms so that it is possible to check afterwards whether the adverse event was caused by rapamycin or the placebo.

A serious adverse event is any untoward medical occurrence or effect that at any dose results in death;

- is life threatening (at the time of the event);
- requires hospitalisation or prolongation of existing inpatients’ hospitalisation;
- results in persistent or significant disability or incapacity;
- is a congenital anomaly or birth defect;
- is a new event of the trial likely to affect the safety of the subjects, such as an unexpected outcome of an adverse reaction, lack of efficacy of an IMP used for the treatment of a life threatening disease, major safety finding from a newly completed animal study, etc.

All SAEs will be reported to the accredited METC that approved the protocol, according to the requirements of that METC.

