13. ANNEXES……………………………………………………………………………………31

**SUMMARY**

**Rationale:** Birt-Hogg-Dubé syndrome (BHD) is a rare autosomal dominant disorder characterized by the occurrence of benign, mostly facial, hair follicle tumours called fibrofolliculoma, multiple lung cysts and (probably as a result) spontaneous pneumothorax and kidney cancer. The fibrofolliculomas can be quite disfiguring and are usually the reason that patients come to medical attention**.**

A topical treatment for chronic use that reduces the number of tumours and/or prevents the growth of new ones would be preferable but is not yet available.

Research on mouse models and our own human data suggest that in BHD syndrome there is deregulation of mTOR signalling. mTOR, mammalian target of rapamycin, is a multiprotein-complex that is a central player in cellular growth regulation and energy sensing. We think that in BHD the mTOR protein is upregulated or overactivated which causes tumour growth, including fibrofolliculomas. This would mean that mTOR inactivation could prevent growth of fibrofolliculomas. New insights from genetic and cell biological studies now suggest a potential therapy; the mTOR inhibitor rapamycin. Rapamycin oral solution has been used topically in previous studies and was both safe and effective. Thus, we have theorized that rapamycin oral solution might be used safely topically for the treatment of BHD-associated fibrofolliculomas.

**Objectives**: Primary objective: To determine whether topical application of rapamycin can lead to reduction in size and/or number of fibrofolliculomas in BHD patients and may prevent the growth of new ones. Secondary Objectives: Safety, formula acceptance and patient satisfaction.

**Study design:**Double-blind placebo-controlled randomized intervention study.

**Study population:** Otherwise healthy patients ≥ 18 years of age with genetically proven Birt-Hogg-Dubé syndrome and facial fibrofolliculomas.

**Intervention**: Application of rapamycin 1 mg/ml oral solution to one predefined skin area on one facial half, twice daily. The other facial half will be similarly treated with a placebo.

**Main study endpoints:** The main study parameter is significant regression (reduction in facial fibrofolliculoma size and count) in the treated area due to topical rapamycin. Secondary endpoints are the absence of any effect, tolerability, adverse events, formula acceptance and patient satisfaction.

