# 3. STUDY DESIGN

The study is double-blind placebo-controlled randomized with the patient him/herself as an internal control. To get enough power we aim to include 20 (see power analysis) adults ≥18 years with Birt-Hogg-Dubé syndrome. Inclusion will take place in two hospitals in the Netherlands; Maastricht University Medical Centre and VU Medical Centre Amsterdam. After inclusion patients are treated with rapamycin in one facial half and a placebo in the other. Patient and physician are blinded until the end of the study. The solution (placebo and verum) is applied according to standardized instructions. The study will proceed according to standardized trial monitor forms (Annex F4). These forms describe how the patient is to be examined at each visit. The skin will be evaluated by 3 observers; the investigator and two dermatologists. They will assess a difference in fibrofolliculoma status on a 7-point rating scale ranging from -3 (strong worsening) to +3 (strong improvement). Although patients evaluate their skin on this scale too, we will not include their measurements in the analysis because of bias. For further explanation see chapter 7.

Patients will be followed-up at 3 months and at 6 months.

It is likely that, during the study, one facial half will improve because of treatment with rapamycin. However, we do not think it is ethical to ask our patients to deal with one improved facial half and one unimproved facial half. Moreover, when patients see a difference between facial sides, they might apply the solution, that they think is the effective one, on both facial sides. To prevent this situation we developed the following study design:

When a clear difference arises between facial sides, blinding will be broken and we will proceed with an open-label study. There are a few conditions to break the blinding, pointed out below.

- Two of three observers have to see a significant difference. This means that there must be an improvement (or worsening, which we don’t expect) of at least 2 points on the 7 point rating scale.
- When there is a significant difference, the blinding will be broken. Then it will also become clear whether the improved side is the rapamycin-treated side. In this case patients are allowed to use rapamycin on the entire face.
- When patients see a difference between the left and right facial side themselves, they can make an earlier appointment.

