# 5. TREATMENT OF SUBJECTS

## 5.1 Investigational product/treatment

Test treatment:

- Rapamune 1 mg/ml
- Active ingredient: rapamycin
- Strength: 0,1%
- Dosage form: oral solution, in this study for topical use
- Manufacturer: Wyeth Pharmaceuticals

After randomisation, patients apply rapamycin 1 mg/ml oral solution (Wyeth) to one predefined skin area on one facial half, twice daily, during 6 months. The other facial half will be similarly treated with a placebo consisting of the excipients only. One of the excipients is propylene glycol which defines the colour (yellowish) and smell of the solution. Because rapamune and placebo solution both contain this substance, the solutions can not be distinguished. For preparing the placebo solution the excipients (polysorbate 80 and Phosal PG 50) will be merged into a container. Later water is added and everything is mixed for 10 minutes. Regarding storage and transport we may state that rapamycine and placebo both will be stored at a temperature of 2-8°C. Bottles will be packed in firm export material (cardboard) so that bottles can impossibly break.

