## 6.4 Summary of known and potential risks and benefits

A potential risk when participating in this study is an allergy for one of the components of rapamune oral solution. We do not foresee any other risks. Prior research has shown that local application is safe and does not lead to significant plasma levels.

A benefit of topical rapamycin is that side effects are negligible. This contrasts with treatments that are used presently, such as laser and surgical interventions. Complications like scar formation, inflammation, hypo- and hyperpigmentation may occur.

Topical application of rapamycin is potentially associated with temporary irritation and a tingling or slightly painful sensation. However, this is likely due to the alcohol in the excipient. These minor side effects can be easily controlled with a fatty ointment.

Other potential benefits are prevention of new tumour growth and reduction in size and/or number of tumours.

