### 7.1.2. Secondary study parameters/endpoints

Secondary parameters/endpoints:

- The absence of any effect.
- Safety, assessed by tolerance and adverse event profiles.
- Acceptance of study medication by subjects, indicated on a 5-point rating scale:

0= not acceptable

1= somewhat acceptable

2= moderately acceptable

3= acceptable

4= very acceptable

Patient satisfaction is assessed on the basis of 3 statements. Here patients can express to what extent they agree with the statement. For the extent of agreement a 5-point rating scale is used ranging from total disagreement (-2) to total agreement (+2).

See also trial monitor forms: Annex F4

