## 7.3 Study procedures

Conduct of the study

The first visit (screening) includes:
- In- or exclusion, in case of inclusion:

- Physical examination according to protocol, especially lesion size and count
- Biopsy of a representative tumour (if not yet undergone one)

- The patient already has the patient information; this has been sent before the first visit.

- For women: pregnancy test

The second visit (baseline) includes:

- Physical examination according to protocol

- Standardized medical photography of the face. (All photos will be assessed by the investigator and two independent physicians).
- Instruction of patient (see Annex E4), provide study medication according to randomization

Follow-up visits will take place at 3 months and at 6 months. At each follow-up visit, unused study medication will be taken back and new medication is dispensed. Unused medication is weighed to ensure protocol compliance.

At the first follow-up visit at 3 months it will be assessed if unblinding is needed.

Physical examination and medical photography are part of regular care/medical treatment.

Treatment with rapamycin solution (and placebo solution) and pregnancy tests are part of the study.

See also trial flow-chart: Annex F4.

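### Tolerability is a secondary endpoint with no stated measure, and passive event collection with visits three months apart is likely to under-record mild, transient local reactions unless Annex F4 asks about them

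*Protocol*

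**What the plan says.** - **Endpoint.** The Summary states: "Secondary endpoints are the absence of any effect, tolerability, adverse events, formula acceptance and patient satisfaction". Section 7.1.2 lists "Safety, assessed by tolerance and adverse event profiles". That section gives 5-point scales for acceptance and for satisfaction, but none for tolerance.
- **Collection rule.** Section 8.2 of the protocol: "All adverse events reported spontaneously by the subject or observed by the" investigator or the investigator's staff will be recorded. It mentions no active questioning, checklist or diary.
- **Side.** Section 8.2 also says: "When a local side effect appears, the affected side of the face will be recorded on the study forms". The stated purpose is to attribute the event to rapamycin or placebo afterwards.
- **Timing.** Section 7.3: "Follow-up visits will take place at 3 months and at 6 months". Section 5.1 has each solution applied "on one facial half, twice daily, during 6 months", and section 6.7 has study medication posted to the patient monthly.
- **Foreseen reactions.** Section 6.4: "Topical application of rapamycin is potentially associated with temporary irritation and a tingling or slightly painful sensation". The same section thinks the alcohol in the excipient the likely cause, and section 5.1 describes the placebo as excipients only.
- **Forms.** Section 3 says of the trial monitor forms in Annex F4: "These forms describe how the patient is to be examined at each visit". Section 7.1.2 also refers to them. Their content is not shown.

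**The concern.** The collection rule suits the foreseen reaction poorly. Staff cannot see tingling or slight pain, and a temporary reaction may have gone by the next visit. What reaches the form then depends on the patient remembering it and choosing to mention it. The side is written down only for events that become known, so a half with no entry could mean no reaction or no question.

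Two things are at stake. First, the split-face design offers a masked vehicle control within each patient, which is the trial's own means of checking whether irritation comes from the excipient. That comparison needs an answer for both halves, including none. Second, sections 6.4 and 9.4 call topical side effects negligible, and section 9.4 relies on this when it omits an interim analysis. Passive collection leans towards confirming that premise whether or not it is true. Once the code is broken and rapamycin may go on the whole face (section 3), the within-patient contrast is lost and earlier gaps cannot be filled.

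**Working it through.** The plan gives no figure for tolerability, so there is none to reproduce. The check is a reading of the sections against each other, followed by two illustrations whose rates are assumptions.

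**1. Is tolerance given a measure?** Section 7.1.2 names tolerance but gives no scale, symptom, time point or side. The acceptance score beside it (0 to 4) mentions neither symptom nor side, so it cannot stand in.

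**2. How long is the recall interval?** Three months is about 365.25 / 4 ≈ 91 days. At two applications a day, 2 × 91 = 182 applications per facial half fall between visits.

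**3. How much could be lost?** Inputs: n = 20 patients (section 4.4). The share of patients with a local reaction, p, and the share of those recorded, c, are assumptions, because the documents give neither. Expected recorded cases = n × p × c. Chance of recording at least one = 1 − (1 − p × c)^n.

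| p | true cases | expected recorded at c = 25%, 50%, 75%, 100% | chance of at least one |
|---|---|---|---|
| 10% | 2 | 0.5, 1.0, 1.5, 2.0 | 0.40, 0.64, 0.79, 0.88 |
| 30% | 6 | 1.5, 3.0, 4.5, 6.0 | 0.79, 0.96, 0.99, above 0.99 |
| 50% | 10 | 2.5, 5.0, 7.5, 10.0 | 0.93 at 25%; above 0.99 from 50% upwards |

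The result depends on c. Most cases are lost only if capture is low.

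**4. Would full capture make the half-to-half comparison firm?** Assume a true rate of 40% on rapamycin halves and 15% on placebo halves, independent of each other, with capture q the same on both. Set r = 0.40q and s = 0.15q. Expected pairs with a recorded reaction on rapamycin only = 20 × r × (1 − s); on placebo only = 20 × s × (1 − r).

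- q = 100%: 20 × 0.40 × 0.85 = 6.8, against 20 × 0.15 × 0.60 = 1.8.
- q = 60%: 20 × 0.24 × 0.91 = 4.4, against 20 × 0.09 × 0.76 = 1.4.
- q = 30%: 20 × 0.12 × 0.955 = 2.3, against 20 × 0.045 × 0.88 = 0.8.

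Rounding the full-capture case to 7 against 2, the exact two-sided McNemar p-value is 2 × (1 + 9 + 36) / 512 = 92 / 512 = 0.18. So even complete collection with a sizeable assumed difference gives no firm test in 20 patients. With equal capture, the ratio of the two recorded rates (0.40q / 0.15q = 2.7) does not depend on q; the level of both rates falls.

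**5. Do these rates fit the protocol?** Not well. If the excipient causes the irritation, as section 6.4 thinks likely, and both halves receive it, the halves should react at similar rates and often together. There would then be fewer discordant pairs than in step 4. That leaves the level of irritation, and its presence or absence on each half, as the main thing to learn.

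**The case against.** The strongest reply is that the Annex F4 forms may already do this. Section 7.1.2 points to them for the secondary endpoints, section 3 says they govern the examination at each visit, and a left/right tolerance item is ordinary form content. This stands, and it makes the finding conditional. It does not explain why 7.1.2 defines scales for acceptance and satisfaction but not for tolerance, or why 8.2 states a passive rule without qualification.

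A reader might infer that the expected stinging will be largely missed. The documents do not support that. Section 6.4 says only that reactions are potentially associated with use. No capture rate is given anywhere. With twice-daily use, stinging may recur and be present or fresh in memory at a visit. Staff can see redness, and section 8.2 foresees irritation reaching the trial physician.

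A reader might also infer that passive collection is what spoils the comparison between halves. Steps 4 and 5 show otherwise: the number of patients limits it, and a shared excipient effect would limit it further.

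It is fair, too, that recording spontaneous and observed events is a recognised method, and that 8.2 does provide for the side once an event is known. What remains is narrower: a named endpoint lacks a stated measure, and the stated rule produces no negative answers.

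**Conclusion.** The point holds as a modest weakness of design, not as an error or contradiction. On the protocol text, tolerability has no defined measure, and mild, transient, subjective local reactions are likely to be under-recorded. No half of the face receives a recorded none. This rests on one assumption that cannot be checked here: that the Annex F4 forms do not already ask about local tolerance by side.

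The size of the under-recording cannot be computed from the documents; the table in step 3 shows only how it varies with assumed rates. The gain from asking is a less biased, side-specific description. It is not a confirmatory comparison, and the primary analysis is unaffected.

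**What to change.** In sections 7.1.2 and 8.2, state that at the 3- and 6-month visits every patient is asked a fixed local-tolerance question covering the period since the last visit. For example: stinging, redness and dryness, each graded none, mild, moderate or severe, and answered separately for LEFT and RIGHT. At a visit where unblinding is considered, ask it before that decision. Use the answers up to any code break as the tolerance endpoint, summarised as within-patient pairs. Keep spontaneous reporting for all other adverse events. If Annex F4 already contains such an item, cite it in both sections and define the endpoint from it.

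A monthly symptom card in the medication parcels would shorten recall, but it is better left out. It would repeatedly prompt patients to compare the two sides, and section 3 worries that patients who see a difference may put the solution they believe effective on both.

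The cost is a short form item at visits already planned. More mild events will be recorded on both halves, and recall over three months remains.

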**Nature and extent of the burden and risks associated with participation, benefit and group relatedness:** Participation requires patients to apply rapamycin liquid and placebo liquid twice daily. Participation in the study will take the patient 5 minutes a day, plus the 4 control visits that will take approximately 30 minutes. A potential risk when participating in this study is an allergy for one of the components of rapamune oral solution. Furthermore, local irritation due to the excipient, which contains alcohol, is possible but this can be easily controlled with emollients. There will be one biopsy for patients who have not yet undergone one. A skin biopsy is taken by means of a 3 mm punch after injection of local anaesthetic which is briefly painful. A properly taken biopsy will leave no or minimal scarring. Previous studies have shown that topical application of rapamycin is safe and does not lead to therapeutic plasma levels. The benefit for the patients is in the potential reduction in facial tumour size and number. For BHD patients in general the benefit will be an easily used topical treatment with which fibrofolliculomas may be treated or prevented.

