## 4.3 Exclusion criteria

Proven or suspected malignancy of skin or other organs. No histological confirmation. Skin lesions other than fibrofolliculomas that might worsen under rapamycin such as active infections. Pregnancy or failure to comply with contraceptive measures. Not able to comprehend instructions. Age under 18 years. No proven mutation. Less than 10 fibrofolliculomas. Planned facial surgery in the treatment period. Concomitant disease requiring systemic immunosuppressive treatment during the trial period or within 30 days before starting therapy. The use of facial topical immunosuppressive treatment or facial topical drugs that interfere with rapamycin during the trial period or within 30 days before starting therapy. Not capable of informed consent. Drug- or alcohol abuse. Tendency to form keloids.

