## 5.2 Use of co-intervention

The use of topical immunosuppressants in the face, including tacrolimus and corticosteroids and the use of any other facial dermatological medication that is interacting rapamycin, is not allowed. Topical medication that is used outside the face can be allowed after consultation with the principal investigator. Oral immunosuppressive medication is not allowed. Any other oral medication is only allowed after consulting the principal investigator.

Females should ensure adequate contraception using oral contraceptives and barrier methods. Local surgical procedures including laser surgery are not allowed. If there is a medical necessity for such procedures the patient must discontinue the trial.

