### 7.1.3. Other study parameters

Other study parameters (baseline characteristics) will be presented in a table.

These other parameters are age, sex, count and average size of FF, previous treatment for FF, age of presentation of FF, other medication used during the trial, medical history.

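### Section 8.2 prescribes a temporary corticosteroid for non-allergic irritation, which section 5.2 forbids without a rescue exception

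*Protocol*

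**What the plan says.** Section 8.2 of the protocol takes local irritation following rapamycin as its example of an adverse reaction. The trial physician consults the principal investigator, and the instruction is: "If this is not allergic, the trial will continue and the patient will get a corticosteroid temporarily". Allergic irritation leads to exclusion instead. No route, duration or facial side is given for the steroid. The section also has the affected side recorded, so that it is "possible to check afterwards whether the adverse event was caused by rapamycin or the placebo".

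Section 5.2 lists what is not allowed. It opens with "The use of topical immunosuppressants in the face, including tacrolimus and corticosteroids" and adds, for the oral route, "Oral immunosuppressive medication is not allowed". It leaves two matters to the principal investigator: topical medication used outside the face, and oral medication other than immunosuppressants.

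Two other places deal with irritation and do not mention a steroid. The summary says "this can be easily controlled with emollients", and section 6.4 says "These minor side effects can be easily controlled with a fatty ointment".

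**The concern.** One section tells the physician to give a corticosteroid and carry on. Another says that a patient in the trial may not have one on the face. The event is not remote: the summary and sections 6.4, 8.2 and 10.3 all foresee local irritation. With two centres, physicians could follow different sections.

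This has a statistical side because each patient is a matched pair of facial halves (sections 3 and 9.2), and response is scored from facial photographs (section 7.1.1). Section 8.2 allows for local effects on one side, since it records the side in order to attribute the event. If the steroid went on that side only, the halves would differ in more than rapamycin versus placebo. The patient's standing is also unclear: compliant under 8.2, in breach under 5.2. Section 9.2 plans both an intention-to-treat and a per-protocol analysis, so the contradiction reaches the second of these.

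**Working it through.** No arithmetic applies. The check is whether any reading of the text lets a physician obey both sections.

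1. **Where the irritation is.** Section 5.1 has rapamycin applied to a predefined area on one facial half and placebo on the other. Local irritation is therefore on the face.
2. **Topical steroid at that site.** Section 5.2 names corticosteroids among the facial topical immunosuppressants that are not allowed. The class is stated, so nothing has to be inferred. Giving it breaks 5.2.
3. **Oral steroid.** Section 5.2 bars oral immunosuppressants. It already treats corticosteroids as immunosuppressants when used topically, so the natural reading includes oral ones. Giving it breaks 5.2.
4. **Discretion of the principal investigator.** The discretion in 5.2 covers topical drugs outside the face and oral drugs that are not immunosuppressants. Neither covers steps 2 or 3.
5. **Medical need for something prohibited.** Section 5.2 addresses this once, for local surgical and laser procedures, and requires the patient to leave the trial. For the steroid, 8.2 says the opposite: the patient stays in.
6. **Rescue exception or cross-reference.** There is none in 5.2, 8.2 does not refer to 5.2, and no other section reconciles them.

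So neither the topical nor the oral route satisfies both sections. This assumes that one of those two routes is meant; 8.2 does not say.

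**What can be said about bias.** Section 6.4 attributes irritation probably to alcohol in the excipient, and section 5.1 makes the placebo from the excipients alone. On that account both halves are exposed to the likely irritant. Section 8.2, by contrast, presents irritation as an example of a reaction to the study drug and provides for one-sided events. The protocol gives no frequency of irritation on either half, no frequency of steroid use, and no information on whether a short steroid course alters fibrofolliculoma size or count. Neither the size nor the direction of an effect can be calculated.

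**The case against.** The best defence is that 8.2 is the specific rule and 5.2 the general one, so 8.2 works as an implied rescue provision, applied after the principal investigator has been consulted. That may well be what was intended. It does not settle the matter, because 5.2 marks out where that discretion applies and facial steroids lie outside it. Even as an exception, 8.2 leaves route and duration open.

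Other parts of the defence stand, and they limit the point.

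- **Section 4.3.** A reader might infer a third conflict, since the exclusion criteria include "The use of facial topical immunosuppressive treatment or facial topical drugs that interfere with rapamycin during the trial period". But 4.3 sets entry criteria, applied at screening (section 7.3), and reads naturally as need foreseen at entry. It is not a withdrawal rule.
- **Emollients and fatty ointment.** A reader might take these as contradicting 8.2. They appear in risk summaries, and 6.4 is describing minor effects. They can be a first step, with the steroid as a later one.
- **Bias for or against rapamycin.** A reader might infer a systematic distortion. The shared excipient argues against assuming one, and nothing in the protocol demonstrates one.
- **Per-protocol decisions.** A reader might infer that these would be made with knowledge of allocation. Section 7.2 already assigns patients to analysis populations before general unblinding. Only patients whose code is broken early, as sections 3 and 7.2 permit, fall outside that safeguard. Detailed membership rules may also be in a statistical analysis plan that is not at hand.

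A statistical analysis plan cannot, however, decide which of two treatment instructions the physician should have followed.

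**Conclusion.** The conflict between sections 8.2 and 5.2 is real and should be removed. It is a contradiction between two operative treatment rules, not a detail left for later, and it concerns an adverse reaction that the protocol itself expects. The conclusion rests on the wording of the two sections and on the assumption that the steroid would be topical on the face or oral.

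The consequence for the comparison is a possibility only. A steroid confined to one facial half would be an unequal co-treatment within that patient's pair. How often this would happen, and which treatment it would favour, cannot be determined from the protocol. No loss of power is claimed, and the number of patients in the intention-to-treat analysis is unaffected.

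**What to change.** Choose one rule and state it the same way in both sections.

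- **Option (a).** Delete the corticosteroid from 8.2 and manage non-allergic irritation with the emollient or fatty ointment already named in the summary and section 6.4. This costs one changed sentence, and removes the steroid as a treatment for irritation within the trial.
- **Option (b).** Add an explicit rescue exception to 5.2, cross-referenced in 8.2, giving the route and a maximum duration. Record any steroid use by facial half with start and stop dates. The affected side (8.2) and "other medication used during the trial" (section 7.1.3) are already to be collected, so this is a small addition to the trial forms.

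The choice is clinical and belongs to the sponsor. Under (b), the arrangement in section 7.2 for assigning analysis populations is sufficient for most patients. For a steroid-treated patient who is unblinded early, add that per-protocol status is settled before the code is opened, or by someone who does not know it. Rewording 4.3 is optional. Either option takes a few lines and needs no change to the sample size or the primary analysis.
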